### Randomization

The random allocation sequence will be computer generated in blocks of four and stratified for gender and degree of disability (modified Rankin scale <3 and ≥3). A sealed, colored envelope will have a serial number on the outside and a folded sheet of paper inside with the group allocation written on it: this will be impossible to read from the outside. The study coordinators will enroll participants and assign them to interventions in order according to the serial number. The random allocation sequence will be computer generated by the study manager who is not involved in the randomization process. Each month, the correct use of envelopes will be controlled for ten patients.

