## Methods/design

### Trial design

A randomized, controlled trial with two parallel groups and an allocation ratio of 1:1.

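### Constant blocks of four, with the same coordinators enrolling and assigning at one hospital, make up to a third of allocations deducible by anyone who tracks the strata

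*Protocol article*

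**What the plan says.** All references are to the protocol article.

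- **Trial design:** "A randomized, controlled trial with two parallel groups and an allocation ratio of 1:1".
- **Randomization, sequence:** the allocation list is "computer generated in blocks of four and stratified for gender and degree of disability". No other block size is given and no variation is mentioned. The strata are gender by modified Rankin scale (below 3, or 3 and above), so there are four. Both factors are known before a patient is allocated.
- **Randomization, roles:** "The study coordinators will enroll participants and assign them to interventions in order according to the serial number". The sequence is "computer generated by the study manager who is not involved in the randomization process".
- **Randomization, safeguards:** the envelopes are sealed and serially numbered, and of the sheet inside the article says "this will be impossible to read from the outside". In addition, "Each month, the correct use of envelopes will be controlled for ten patients".
- **Participants:** one hospital serves the whole county.
- **Interventions:** one arm receives nurse telephone contact and adjustment of medication. The other receives usual care with nothing added by the study. No masking is described.
- **Statistical methods:** the primary model adjusts for gender and degree of disability. Adjustment for further baseline covariates is planned as an additional exploratory analysis.
- **Discussion:** county-wide eligibility is said to avoid selection bias.
- **Trial status:** the trial is described as ongoing, with no statement on whether recruitment is open.

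**The concern.** In a permuted block of constant, known size, the last allocations follow from the earlier ones. This matters most when the arms are visible, when all allocations in a stratum pass through one local team, and when the people who enrol also see what each patient was assigned. All three conditions are stated in the article or follow directly from it.

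At stake is the comparability of the arms. Some entry criteria need judgement, such as whether a patient can manage telephone contact or has severe disease. If the next arm is known, an approach to a patient can be delayed or left out according to that arm, for reasons such as frailty or expected adherence. Such factors could plausibly relate to systolic blood pressure at 36 months. The primary model adjusts only for the stratification factors and would not correct for this.

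**Working it through.** The article states no predictability figure, so there is none to reproduce.

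**Inputs.** Block size 4 and four strata (Randomization); 1:1 allocation, hence two per arm in each block (Trial design); at least 200 per group, about 400 in total (Sample size).

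**Step 1: allocations that are certain.** A block with two A and two B has 4!/(2!·2!) = 6 equally likely orders. An allocation is certain when only one arm is left in the block.
- Positions 1 and 2: never certain.
- Position 3: certain when the first two match (AABB, BBAA), probability 2/6 = 1/3.
- Position 4: always certain.

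Expected number certain per block = 1/3 + 1 = 4/3. As a share, (4/3)/4 = 33.3%. For 400 patients, 400/3 ≈ 133.

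**Step 2: unfinished last blocks.** A simulation of 400 patients in four strata, with assumed stratum shares of 40, 35, 12 and 13% (the article gives none), yields 32.9%, about 132 patients. Incomplete blocks hardly matter.

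**Step 3: best guess.** The best strategy names the arm with more places left in the block.
- Position 1: 1/2.
- Position 2: 2/3.
- Position 3: (1/3)·1 + (2/3)·(1/2) = 2/3.
- Position 4: 1.

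Average = (1/2 + 2/3 + 2/3 + 1)/4 = 70.8%, against 50% by chance.

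**Step 4: alternatives.** The fixed sizes come from the same enumeration. The varying sizes come from a simulation of an observer who knows the set of sizes but not the one drawn, and who updates on every allocation.

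| Scheme | Certain | Best guess correct |
|---|---|---|
| Fixed 4 | 33.3% | 70.8% |
| Fixed 6 | 25.0% | 68.3% |
| Fixed 8 | 20.0% | 66.6% |
| Random 4/6/8, size drawn concealed | about 2% (2.3 to 2.5% across runs) | about 68% |

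Varying the size removes nearly all the certainty, from about 133 allocations to about 9 or 10 of 400. It leaves most of the guessing advantage.

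**Step 5: the stated safeguards.** Envelopes that cannot be read protect against reading. Separate sequence generation protects against the enroller holding the list. The monthly check protects against envelopes used out of order. A coordinator who delays or does not approach a patient still uses every envelope correctly, so none of the three detects or prevents deduction.

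**The case against.** The strongest reply is that one third is a ceiling. It needs a coordinator who knows the block size, sees every earlier allocation in the stratum, including those made by colleagues, and keeps the place in four interleaved sequences. The article does not say that the coordinators were told the block size. This stands: the figure is what could be deduced. A reader might infer that a third of allocations were in fact known, or that the comparison is biased; the document supports neither.

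A reader might also infer that the coordinators judge eligibility, take consent and open the envelopes. The article says only that they enrol and assign. It describes consent without naming a role and does not say who judges eligibility. The point does not depend on this, because control over enrolment is enough.

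Publishing the block size while the trial is ongoing might be read as having made prediction easier during recruitment. With 36 months of follow-up, an ongoing trial may already have finished enrolling, so that does not follow.

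There are further safeguards. Possible cases are identified from brain computed tomography, the logistics aim to include every stroke and TIA patient, and several exclusions are concrete (aphasia, dementia, deafness, another trial). These narrow the room to act on a prediction and could make arm-dependent non-enrolment more visible, but they do not stop deduction. The exploratory covariate adjustment under Statistical methods also bears on this, but it reaches only imbalance in measured covariates.

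Finally, the effect on the primary outcome has not been sized, and the document gives nothing from which to size it.

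**Conclusion.** The point holds as an avoidable design weakness. Constant blocks of four in four strata at one hospital, without described masking and with enrolment and assignment in one role, allow up to 33.3% of allocations (about 133 of 400) to be deduced with certainty. This assumes that the observer knows the block size and tracks each stratum; the share is lower if strata are not tracked separately. The consequence is a risk of selection bias at enrolment, of unknown size and not demonstrated. The Discussion's statement about avoiding selection bias rests on who is assessed in the county. It does not cover differential enrolment by arm.

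**What to change.** **If recruitment is still open:** for all unused envelopes, generate permuted blocks of randomly varying size (for example 4, 6 and 8) within the same four strata. Only the study manager should know the sizes, and they should not be published until recruitment ends.

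**Cost:** the remaining list and envelopes must be regenerated. The largest possible imbalance within a stratum is half the largest block, so it rises from 2 to 4. Over four strata the worst case rises from 4 × 2 = 8 to 4 × 4 = 16. Even 208 against 192 patients raises the variance of the group difference only by the factor (200 × 200)/(208 × 192) = 1.0016. The primary model already adjusts for both stratification factors. The gain is the removal of certainty; the guessing advantage changes little.

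**If recruitment has closed:** report the predictability as a limitation, and do not rely on the Discussion's claim about selection bias for the comparison between arms.

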### Statistical methods

The primary analysis will be performed according to the intention-to-treat principle using a linear regression model adjusting for gender and degree of disability. The adjustment is made in order to reflect the stratified randomization process. Per protocol analyses will also be performed. Secondary outcomes will be analyzed using the primary analysis model when continuous, and using a logistic regression model, adjusting for the same covariates, when outcomes are binary. In order to assess whether there are indications of differential treatment effects across subgroups (age, gender, co-morbidity, level of education and social classification), tests for interaction will be performed, although this aim is secondary because the study is not powered for this particular purpose. Adjustment for relevant baseline covariates will be performed in additional exploratory analyses of primary and secondary outcomes in order to evaluate the effect of possible baseline imbalance. All tests will be two-sided and a *P*-value of <0.05 will be considered significant.

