## Background

The risk of stroke recurrence, myocardial infarction and death after stroke is high [1,2]. Secondary prevention after stroke is essential in order to reduce morbidity and mortality, consequently leading to reduced costs to society. There are a number of evidence based treatment strategies for secondary prevention after stroke [3]. Risk factor modification may reduce the risk of stroke recurrence by up to 80% [4]. Despite these facts, secondary stroke prevention studies have mostly been performed as clinical trials with non-representative patient selection, for example concerning age and co-morbidity [5]. There is considerable literature about non-pharmacological interventions but a paucity of data concerning the implementation of proven pharmacological interventions in patients representative of clinical praxis [6]. The number of long-term follow-up studies of secondary prevention after stroke is, to date, limited.

The implementation of risk factor intervention after stroke is difficult. There are limitations in terms of compliance and the proportion of patients achieving set treatment goals in usual care [5,7]. Even though adherence to prescribed medication may be quite high in some cohorts of stroke patients [8], the proportion achieving set treatment goals among the various risk factors has been less studied. A strategy to improve secondary prevention results by early interventions shows potential [9]. On the other hand, there is evidence that even high quality secondary preventive measures initiated while patients are hospitalized are no guarantee of a successful outcome after discharge [10]. Further research in this area is essential.

There is limited evidence that nurse-led follow up for risk factor improvement after stroke has a positive outcome [11]. In order to improve secondary prevention after stroke, we have designed a trial with the following components:

1. Population-based. All patients in the county of Jämtland, Sweden, admitted to the county hospital with transient ischemic attack (TIA) or stroke will be considered for inclusion in the study, regardless of age, gender or co-morbidity.

2. The study will be randomized with a nurse-led intervention group and a control group being seen by their general practitioner for usual medical care.

3. The intervention is based on telephone follow-ups by a stroke nurse, in order to facilitate implementation and minimize the necessary resources.

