### Outcomes

Outcomes will be measured after 12, 24 and 36 months of follow-up. Outcome variables are sitting systolic and diastolic blood pressure, LDL cholesterol and total cholesterol, as well as the proportion of patients achieving the set target for these variables. Standing systolic and diastolic blood pressure, smoking rates, the proportion of patients treated with different secondary preventive drugs, diabetes control by Hb1C, change in body mass index (BMI) and physical activity will also be measured. Sitting systolic blood pressure at 36 months will be analyzed as the primary outcome. The analyses of the secondary outcomes will be exploratory.

Blood pressures measurements are standardized as described above. LDL values are calculated from the serum concentrations of cholesterol and fasting triglycerides using the Friedewald formula. Smoking (yes/no) and physical activity (duration/week) are self-reported. Deaths are available in the hospital records and will be recorded in order to detect any survival difference between groups.

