### Sample size

To reliably detect a difference between groups in mean systolic blood pressure of 5 mmHg requires study groups of 180 participants (standard deviation 19, mean systolic blood pressure 140 versus 135, alpha 0.05 two-tailed, power 80%). Study groups of at least 200 participants are planned to allow for drop-outs. This sample size is also adequate for detection of clinically meaningful group differences in lipid values (0.3 mmol/l, standard deviation 1.0), smoking rates (10%), proportion reaching treatment goals (10%), change in BMI (1.0, standard deviation 4.0) and change in physical activity (10%, proportion in a given activity level), calculated with two-tailed alpha 0.05, power 80%.

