## Discussion

Stroke is one of the major diseases in the current ageing population, with substantial consequences for individuals and society. The knowledge of secondary preventive measures to prevent further disease in stroke patients is strikingly low. Further research in the areas of compliance, the possibility of participation in secondary preventive studies and the possibility of reaching treatment goals in a cohort of stroke patients representative for clinical praxis is absolutely necessary.

This study covers all patients in one Swedish county, who after TIA or stroke, will be eligible for inclusion, thus avoiding selection bias. This allows us to study even very old and very sick stroke patients, who are usually not included in randomized stroke studies. Their ability to participate in secondary prevention programs and their tolerability of medication when attempting to achieve set treatment goals are of great interest as these have significant consequences for health economics and mortality and morbidity rates.

The study design has several other advantages. Randomization of the patients soon after the stroke or TIA allows us to study the acute phase as well as to perform a long-term follow-up. By establishing an early contact, no patient is expected to be lost to follow-up. The immediate recruitment and the logistics to include each and every stroke and TIA patient will show the true proportion of possible participants in the secondary preventive program.

As it is well known that information and team rehabilitation after stroke affects the outcome, the study is designed so that each eligible patient will receive the same present standard of care regardless of randomization group.

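### As written, the intention-to-treat regression uses only patients with a 36-month pressure; bringing the 12- and 24-month readings into it is a cheap safeguard, and the statements on loss need reconciling.

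*Protocol article*

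**What the plan says.** The primary endpoint is a single time point (Outcomes): "Sitting systolic blood pressure at 36 months will be analyzed as the primary outcome". The same pressure is also read earlier: "Outcomes will be measured after 12, 24 and 36 months of follow-up". Of everything other than the primary outcome, the section says: "The analyses of the secondary outcomes will be exploratory".

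Statistical methods names the principle and the model: "The primary analysis will be performed according to the intention-to-treat principle using a linear regression model". The only covariates are the two stratification factors: "using a linear regression model adjusting for gender and degree of disability". Earlier pressure is not in the model, and the article does not say how a randomized patient without a 36-month reading is handled.

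On loss, the article says different things in different places:
- Discussion: "By establishing an early contact, no patient is expected to be lost to follow-up".
- Sample size: "Study groups of at least 200 participants are planned to allow for drop-outs".
- Background: "The risk of stroke recurrence, myocardial infarction and death after stroke is high".
- Outcomes also states that deaths will be recorded to look for a survival difference. The Discussion presents the inclusion of very old and very sick patients as a strength.

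**The concern.** A regression on the 36-month value has nothing to fit for a patient who lacks that value. Gender and disability stratum say little about what that patient's pressure would have been. Unless something is added, a model labelled intention-to-treat therefore becomes an analysis of those still measured at three years.

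The design makes arm-dependent loss plausible, though it does not establish it. Scheduled contacts at one, 12, 24 and 36 months are the same in both arms. Intervention patients above target are also retested within about four weeks and have their treatment adjusted, while controls get no additional intervention from the study. The difference in contact is therefore largest among poorly controlled patients. If such patients leave one arm more readily than the other, the 36-month comparison is distorted. The readings that would correct much of this are already scheduled in both arms.

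**Working it through.** **1. The plan's own figures.** The inputs from Sample size are a 5 mmHg difference, SD 19, two-tailed alpha 0.05, 80% power, 180 required and 200 planned per group.

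- Implied loss allowance: 1 − 180/200 = 10%. The article states no rate.
- Required n: 2 × (1.960 + 0.842)² × 19² / 5² = 226.7, so 227 per group. The stated 180 does not reproduce. It matches a one-sided test (179). This is a separate matter, but it affects how power should be read here.

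**2. Power against numbers measured.** Power = Φ(5 / (19 × √(2/n)) − 1.96).

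| Missing at 36 months | n per arm | Power |
|---|---|---|
| 0% | 200 | Φ(2.632 − 1.960) = 74.9% |
| 10% | 180 | Φ(2.497 − 1.960) = 70.4% |
| 20% | 160 | 65.3% |
| 30% | 140 | 59.6% |

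The planned 10% loss costs 74.9 − 70.4 = 4.5 points. The rest of the gap to 80% is there with nobody missing.

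**3. Bias of the complete-case difference.** Three inputs are not in the documents and are assumed: the proportion missing (10, 20 or 30%, equal in both arms), the correlation ρ between 24- and 36-month pressure (0.5 to 0.6), and the log-odds of loss per mmHg of 24-month pressure.

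Let z be the standardized 24-month pressure in an arm. The shift in that arm's 36-month mean is ρ × 19 × E[z | retained], with E[z | retained] obtained by integrating over a logistic drop-out curve. A slope of 0.04 per mmHg is 0.76 per SD, and 0.02 is 0.38 per SD.

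| Missing | E[z], slope 0.04 | E[z], slope 0.02 | Controls only (0.04 v 0) | Partly differential (0.04 v 0.02) |
|---|---|---|---|---|
| 10% | −0.072 | −0.038 | 0.7–0.8 mmHg | 0.3–0.4 mmHg |
| 20% | −0.139 | −0.074 | 1.3–1.6 mmHg | 0.6–0.7 mmHg |
| 30% | −0.205 | −0.111 | 1.9–2.3 mmHg | 0.9–1.1 mmHg |

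Example (30%, ρ = 0.6, controls only): 0.6 × 19 × 0.2049 = 2.3 mmHg. The control mean is pulled down, so the difference shrinks toward zero.

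With the same slope and the same proportion missing in both arms, the shifts cancel and the bias is near zero. With one common drop-out function of absolute pressure in both arms, it is about 0.1 to 0.3 mmHg.

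The direction follows from which arm is assumed to lose its poorly controlled patients. In a simulation with the pressure-related loss placed in the intervention arm (log-odds 1 per SD, 15 to 25% missing, ρ 0.4 to 0.6), the effect was overstated by about 1.0 to 2.3 mmHg.

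**4. What the earlier reading buys.** Simulation used 200 per arm and predicted the 36-month mean in each arm from the 24-month reading. Remaining bias was about 0.1 mmHg or less in the scenarios of step 3, and at most 0.15 mmHg in the intervention-arm scenario. When loss is unrelated to pressure, neither estimate is biased beyond simulation error, and the standard error falls by about 1 to 5% (for example 2.13 to 2.03). These simulations are missing at random by construction and assume that the 24-month reading is available.

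**The case against.** The strongest reply is that the article names a principle and a model and is silent on missing values. The same regression can be run after multiple imputation, and a full protocol or analysis plan, not shown, may specify that. This stands as far as it goes. It would be wrong to say that the analysis can only use patients measured at 36 months; the supportable statement is that, as written, it does. The absence of missing-data detail is not itself the point. The point is that a better use of scheduled data is available within the stated primary test.

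A reader might also infer that the model was chosen because nobody was expected to be lost, and that the interim readings are ignored. The text supports neither. Statistical methods gives no such reason, Sample size provides for drop-outs, and the 12- and 24-month pressures are analysed as separate exploratory outcomes. Loss to follow-up can also mean lost contact, as distinct from withdrawal or death, so the conflict between sections may be partly one of wording. It still needs settling.

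Third, a single-time-point regression adjusted for the stratification factors is a legitimate prespecified analysis, and the larger biases come from an extreme scenario in which only one arm's loss depends on pressure. Both statements are true, which is why the point is an improvement and not an error.

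Last, the attrition that the article itself points to is death, and a mixed model does not make a pressure after death meaningful. That also stands and limits what the remedy can do.

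**Conclusion.** The point holds as a low-cost improvement plus a wording conflict. As written, the primary model uses only patients with a 36-month pressure, and the expectation of no loss sits badly with the drop-out allowance and the recording of deaths.

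The bias is conditional. It is near zero if loss depends on pressure equally in both arms. If loss is more pressure-related in controls, it runs from about 0.3 mmHg (10% missing, partly differential) to 2.3 mmHg (30% missing, controls only) toward the null, against a 5 mmHg target. The loss rate, the correlation and the drop-out slopes are all assumptions.

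The case for change is protection against bias; the precision gain is only a few percent of the standard error. A reader might take power of roughly 70, 65 and 60% at 10, 20 and 30% missing as the price of attrition. That is not supported: power is already about 75% with all 200 per arm measured, because the stated sample size does not match a two-tailed test, and the planned 10% loss costs about 4.5 points.

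**What to change.** - Keep the treatment contrast at 36 months as the primary test. Estimate it with a model that uses the 12- and 24-month readings: either a repeated-measures mixed model with treatment by visit, gender and disability, or the stated regression after multiple imputation from earlier readings. Include every randomized patient with any follow-up reading.
- If the one-month reading is used, say how patients without it are handled, so that they are not dropped. It is taken after randomization, though before the first intervention call.
- Report deaths by arm, say how death is treated in the primary question, and show the stated 36-month regression in survivors alongside.
- Reconcile the Discussion's expectation of no loss with the drop-out allowance in Sample size and the recording of deaths in Outcomes.

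The cost is wording and some analysis time; the readings are already scheduled in both arms. The downside is that the model assumes missing at random and implicitly projects pressure past death, which is why the survivor analysis has to stand beside it. Patients with no follow-up reading remain outside the mixed model and should be counted by arm.

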### Interventions

All eligible patients will be informed about the study and asked to give a written informed consent. They will receive standard information about stroke concerning the pathophysiology and risk factors according to established clinical praxis during their hospitalization. They will also be offered a follow-up visit to a stroke nurse and an outpatient follow-up according to normal care procedures.

Patients randomized to the intervention group will be contacted by a study nurse by phone one month after discharge. Before the call, a blood sample for lipids will be taken and a standardized blood pressure control will be performed. Blood pressure will be measured after five minutes in the sitting position and after one minute standing. The tests will be performed by a district nurse, or, for patients in the intervention group living close to the hospital, by a study nurse. Self-reported compliance with medication will be recorded. During the call the patient will be informed about the test results and whether a change in medication is necessary. Tobacco use, physical activity and dietary habits will be discussed. Smoking cessation will be encouraged and supported. Physical activity of moderate intensity for 30 minutes or more, most days of the week will be encouraged, but also adjusted to the individual patient’s capacity. Dietary advice to reduce saturated fat and increase the intake of fruit and vegetables will be given. If the patient’s cholesterol or blood pressure values are higher than anticipated, medication will be adjusted after contact from a study physician. Repeated tests will be taken within approximately four weeks and further adjustments made if necessary until target values are reached or no further changes can be considered realistic. The same routine, with an Hb1C test added, will be applied after 12, 24 and 36 months.

The target values are: blood pressure <140/<90 mmHg (optionally <130/<80 mmHg in patients at very high risk, that is, diabetic subjects), total cholesterol <4.5 mmol/l, LDL <2.5 mmol/l [13,14].

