Patients randomized to the usual care group will also be contacted by phone one month following discharge after blood pressure and lipid profile have been checked. Self-reported compliance, tobacco use and physical activity will be recorded. All medical care will be given by their treating physician, usually a general practitioner, who will receive the test results (lipid profile and blood pressure), and no additional intervention will be given as a result of participation in the study. The same routine, with an Hb1C test added, will be applied after 12, 24 and 36 months, Figure 1.

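### The primary model omits the systolic pressure that both arms have before the first study call, and so gives up precision (without causing bias) in a test that falls short of its stated power

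*Protocol article*

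**What the plan says.** The Outcomes section of the protocol article fixes the endpoint: "Sitting systolic blood pressure at 36 months will be analyzed as the primary outcome". Under Statistical methods, the intention-to-treat analysis is done "using a linear regression model adjusting for gender and degree of disability", and the reason is given: "The adjustment is made in order to reflect the stratified randomization process". Continuous secondary outcomes use the same model. Other covariates are placed outside the primary analysis: "Adjustment for relevant baseline covariates will be performed in additional exploratory analyses of primary and secondary outcomes", with the aim of looking at possible baseline imbalance.

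The Interventions section shows that both arms have an earlier reading. For the intervention arm, one month after discharge: "Before the call, a blood sample for lipids will be taken and a standardized blood pressure control will be performed". Control patients "will also be contacted by phone one month following discharge after blood pressure and lipid profile have been checked". The blood pressure procedure includes a sitting measurement, and the Outcomes section refers back to it as the standard. Changes to medication in the intervention arm are made in response to these results, so the one-month reading precedes any study-driven change. Up to that point the article describes the same hospital information and the same follow-up offers for all eligible patients.

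**The concern.** An earlier value of the outcome is a natural covariate when the outcome is continuous, and here the trial already collects one in both arms. Without it, variation in the 36-month pressure that the earlier pressure could explain stays in the residual, and the standard error of the treatment effect is larger than it need be.

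This matters more than usual because the precision is needed. The Sample size section claims 80% power at 180 per group, but its stated inputs do not deliver that. The calculation uses the raw SD of 19, so no gain from covariates has already been counted. At stake is the chance that a true 5 mmHg difference is missed.

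**Working it through.** **Inputs.** Sample size section: difference 5 mmHg (140 versus 135), SD 19, alpha 0.05 two-tailed, power 80%, 180 per group required, at least 200 planned. Trial design section: allocation 1:1. The correlation ρ between the one-month and 36-month systolic pressure is not in the article. It is an assumption here, shown from 0.2 to 0.6.

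**Step 1: the plan's own figure.** For two means, n per group = 2 × [SD × (z for alpha + z for power) / difference]².

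- Two-tailed: 2 × [19 × (1.960 + 0.842) / 5]² ≈ 226.7, so 227 per group. The stated 180 is not reproduced.
- One-sided at 0.05: 2 × [19 × (1.645 + 0.842) / 5]² gives 179 per group. The stated 180 therefore matches a one-sided calculation, although the text says two-tailed.

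**Step 2: power of the planned test without the earlier reading.** Power ≈ Φ(difference / SE − 1.960), with SE = 19 × √(2/n).

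- n = 180: SE = 2.003; 5/2.003 = 2.497; power 70.4%.
- n = 200: SE = 1.900; 5/1.900 = 2.632; power 74.9%.

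A noncentral-t check gives 70.2% and 74.7%.

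**Step 3: power with the earlier reading in the model.** Residual SD = 19 × √(1 − ρ²). For example, at ρ = 0.5 it is 19 × √0.75 = 16.45. At n = 180, SE = 16.45 × √(2/180) = 1.734, 5/1.734 = 2.883, and power is 82.2%.

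| ρ (assumed) | Residual SD | n per group for 80% | Power at 180 | Power at 200 |
|---|---|---|---|---|
| 0 (not adjusted) | 19.00 | 227 | 70.4% | 74.9% |
| 0.2 | 18.62 | 218 | 72.2% | 76.6% |
| 0.3 | 18.12 | 207 | 74.4% | 78.8% |
| 0.4 | 17.41 | 191 | 77.8% | 81.9% |
| 0.5 | 16.45 | 171 | 82.2% | 86.0% |
| 0.6 | 15.20 | 146 | 87.7% | 90.8% |

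**Step 4: correlation at which 80% is reached.** Setting 226.7 × (1 − ρ²) = n gives ρ = √(1 − n/226.7).

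- n = 180: √(1 − 0.794) ≈ 0.45.
- n = 200: √(1 − 0.882) ≈ 0.34.

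**Step 5: which outcomes have a one-month value in both arms.** Blood pressure and lipids do. Hb1C is added to the routine only at 12, 24 and 36 months. BMI is not listed among the one-month measurements in either arm.

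**The case against.** The strongest reply is that nothing in the primary model is invalid. A pre-specified linear model with the stratification factors estimates the randomized effect without bias. A reader might infer from the omission that the estimate is biased by chance imbalance in blood pressure. The article does not support that: chance imbalance is already reflected in the standard error, and the cost is precision only. A reader might also infer that the exploratory adjusted analyses leave the trial without one primary estimate. They do not, because the article names one primary model and ranks the others below it. Which covariates those analyses use is detail that an article may leave to a fuller document.

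The second reply concerns the covariate. Patients are included during the hospital stay, so the one-month reading follows randomization in a trial where the groups are managed visibly differently. The Interventions section also has a district nurse take the measurements, except that a study nurse may do so for intervention patients who live near the hospital. Who measures can therefore differ by arm. With a slope b on the one-month value, an average between-arm measurement difference of d mmHg at one month would shift the adjusted effect by about b × d. This objection stands as a condition on the fix. The same routine is applied at 36 months, so a difference in who measures could also reach the outcome itself under either model. The article does not allow its size to be worked out.

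Third, the gain depends on an unknown correlation over almost three years, with pressure managed toward a target in one arm in between. A low value is possible, and at 0.2 power at 180 rises only from about 70% to 72%. Fourth, the root of the shortfall is the sample size, and 200 per group is a minimum, so larger enrolment would lessen it. Both points stand and limit what the covariate can be said to repair.

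**Conclusion.** The point holds as a matter of efficiency. The primary model omits an earlier value of its own outcome that both arms have, and the test it serves has about 70% power at 180 per group and 75% at 200 on the stated two-tailed inputs. Adjustment raises power at every correlation in the assumed range: by about 2 percentage points at ρ = 0.2, and by 17 at 180 per group or 16 at 200 at ρ = 0.6.

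Two stronger conclusions are not supported. The first is that adjustment repairs the power: it does so alone only if the correlation is about 0.45 or more at 180 per group, or 0.34 or more at 200, and the article gives no value. The second is that every continuous secondary outcome can be treated likewise, since Hb1C and BMI have no described one-month value in both arms.

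The figures assume that the SD of 19 applies at 36 months, that ρ is the within-arm correlation, and that gender and disability explain little further variance.

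**What to change.** Before any analysis by arm, amend Statistical methods so that the primary model for 36-month sitting systolic pressure contains treatment, gender, disability stratum and pre-intervention sitting systolic pressure as a continuous covariate.

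- **Which reading.** Use an in-hospital value from before randomization if one is recorded; the article does not describe one. Otherwise use the one-month value taken before the first study call.
- **Missing covariate values.** Impute them without regard to arm.
- **Secondary outcomes.** Add the one-month value of the same variable for diastolic pressure, LDL and total cholesterol. Do not extend this to Hb1C or BMI.
- **Sensitivity analysis.** Keep the gender-and-disability model and report it alongside.
- **Condition.** If the one-month reading is used, have it taken the same way, by the same type of nurse, in both arms. If that cannot be assured, the adjusted model should not be primary.

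The cost is a sentence or two of text, a rule for missing values and, for the one-month reading, agreement on who measures. No additional variable has to be collected. The Sample size section still needs its own correction, because this change may not close the gap.
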